## Methods/Design

### Study design

The effectiveness of the intervention will be tested in an RCT with two arms, an intervention group and a control group (see Fig. 1). The intervention effects will be tested at two, six, and twelfth months after the start of the intervention. Participants will be 140 adolescents with mild to borderline ID and behavioral problems receiving treatment in treatment facilities. The adolescents will be randomly assigned to the intervention condition (Take it personal!; n = 70) or the control condition (care as usual; n = 70). Recruitment, inclusion, and randomization of the participants will start in the beginning of 2015. The program will start in the spring of 2015 and will continue until the end of 2015. This trial is registered at the Dutch trial register (trial registration: Dutch Trial Register NTR5037. Registered 15 April 2015). The trial has approval of the faculty Ethics Committee of the Radboud University (number: ECSW2015-0903-303).

**Fig. 1 Fig1:**
[figure not shown]
Study design

## Participants

### Recruitment

‘Take it personal!’ was developed for adolescents (14–21 years) with mild to borderline ID who are admitted to treatment centers in the Netherlands. These adolescents often have severe internalizing (anxiety, depression) and externalizing (aggression, antisocial behavior) behavioral problems or psychiatric diagnoses. Participants will be recruited through treatment centers. About ten treatment centers in the Netherlands will be invited to participate in this RCT. These treatment centers offer specialized residential and extramural care for adolescents with mild to borderline ID and severe behavioral problems. A team of therapists will implement the intervention and behavioral scientists and participating institutions will receive the materials for ‘Take it personal!’ free of charge.

After selecting the treatment centers, adolescents will complete a screening questionnaire to identify adolescents who meet the inclusionary criteria. Adolescents will be eligible to enter the trial if they meet the following inclusion criteria: (1) life time prevalence of alcohol, cannabis, or hard drug use, (2) belonging to one of the four personality high-risk groups (SS, IMP, AS or NT), and (3) providing signed informed consent along with the signed informed consent from parents or legal representative. Adolescents scoring more than one standard deviation above the sample mean on one of the four high-risk personality scales of the Substance Use Risk Profile Scale (SURPS) [40] will be classified as belonging to that risk profile. Adolescents who will score above the average on more than one personality profile will be assigned to the profile for which they showed the largest statistical deviation with respect to the z-score (cf. [17]). Adolescents with addiction problems will be excluded from participation in the intervention and the trial because this intervention is not considered sufficient for them. For these adolescents, treatment will be organized in collaboration with a regional institute for addiction care. Parents or legal representatives will be informed about the study through a letter sent home, asking them to contact the researchers by phone or email if they do not wish their child to participate in the screening (passive informed consent). Adolescents will be informed on the day of the screening, at which time they have the option not to participate in the trial. Parents (when participants are under the age of 18 years) and adolescents will need to provide active informed consent to participate in the RCT. After the screening questionnaire and informed consent, the adolescents will be individually randomized to either control condition or experimental condition.

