### Power analyses

In the present study, we aimed to show a medium effect size (cf. [14]). Power-analysis was conducted based on an average effect size of f = 0.25 [41], a 2-sided test at alpha = .05, a statistical power (1-beta) of 0.80, and 10 % loss-to-follow-up after randomization. Based on these assumptions a sample size of 140 adolescents (70 in each condition; G-power) is required. Eighteen intervention groups are required, assuming that up to a maximum of four participants will be included in intervention group.

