Adolescents assigned to the control group will receive no further intervention, but they will receive ‘care as usual’. ‘Care as usual’ will not be standardized or protocolled, but we will make an inventory of other prevention and intervention programs aimed at substance use. Most adolescents receive treatment for their own specific problems; some of them receive residential care while others receive extramural treatment. In both cases, treatment is formulated through personal goals in a so called ‘individual treatment plan’. A multidisciplinary team is involved in the treatment of each adolescent. All participating adolescents will be rewarded with a small gift.

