### Statistical analysis

Descriptive analyses will be conducted to examine whether the randomization results in a similar distribution of demographic factors and outcome measures in both conditions. Variables that show different distributions between the two groups will be entered as confounders in all models testing the effectiveness of the intervention. The effect of the intervention program on the primary and secondary outcome variables will be tested in accordance with the intention-to-treat principle and in a completers-only framework by using Mplus [50]. Intention-to-treat means that all participants will be analyzed in the condition to which they will be assigned by randomization. Missing data will be handled by multiple imputation (MI). A total of 20 datasets will be completed by multiple imputation. Mplus will read the 20 datasets via the TYPE = IMPUTATION option and will carry out the desired analyses for each dataset. Mediating the parameter estimates will then aggregate the results for the 20 analyses. With respect to the completers-only analyses, only the participants with scores for all time points will be included. In both the intention-to-treat and the completers-only analyses, the effect of the intervention condition will be compared to the control condition. Because the data have a multilevel structure (i.e., individuals are ‘clustered’ within treatment centres), the individual respondents within treatment centres may be interdependent. To correct for the potential non-independence (complexity) of the data, the TYPE = COMPLEX procedure in Mplus will be used. This procedure corrects the standard errors of the parameter estimates for dependency, leading to unbiased estimates. The results of the study will be reported in accordance with the CONSORT statement [51, 52].

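### Centre and personality profile are known before allocation, but the stated covariate rule lets them into the effect models only if the arms happen to differ on them

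*Protocol article*

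**What the plan says.** **Allocation (Recruitment).** "After the screening questionnaire and informed consent, the adolescents will be individually randomized to either control condition or experimental condition". This fixes the unit and the timing. It neither mentions nor excludes blocking, stratification or minimisation. "About ten treatment centers in the Netherlands will be invited to participate in this RCT". Profile is an inclusion criterion taken from the screening questionnaire (SURPS), with a cut-off of one SD above the sample mean.

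**Relevance of the two factors.** The Background ties each profile to its own pattern of use and motives, and the Intervention section makes profile decide which of four programme versions is given. On centre, the Statistical analysis section says that "individual respondents within treatment centres may be interdependent". Usual care is not standardised, and of the adolescents in treatment "some of them receive residential care while others receive extramural treatment".

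**Analysis (Statistical analysis).** The balance check is worded thus: "Descriptive analyses will be conducted to examine whether the randomization results in a similar distribution of demographic factors and outcome measures in both conditions". Whatever is found to differ then goes into all effectiveness models as a confounder. Clustering by centre is handled with the TYPE = COMPLEX option in Mplus, which the article describes as a correction of standard errors. No term for centre or profile is stated.

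**The concern.** The rule picks covariates by observed imbalance. A prognostic factor earns its place in a model because it explains outcome, and that is known beforehand; how far the arms differ on it by chance is a poor guide. Under the stated rule the final model depends on the data. The check is also worded for demographic factors and outcome measures, so it is unclear whether centre or profile would be examined at all.

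A standard-error correction for centre does not replace a centre term. It changes the stated uncertainty and leaves the effect estimate as it was, so between-centre differences in use are not taken out of the treatment contrast. If allocation is in fact stratified, the analysis should reflect that; if it is not, the terms are the only protection left. The analysis text needs correcting either way. At stake is some power in a trial sized at its 80% target, and an analysis model that is not fixed in advance.

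**Working it through.** **1. The plan's own figure.** Inputs from Power analyses: "Power-analysis was conducted based on an average effect size of f = 0.25", and "a 2-sided test at alpha = .05, a statistical power (1-beta) of 0.80, and 10 % loss-to-follow-up after randomization". For two groups d = 2f = 0.5. Per arm n = 2(1.96 + 0.842)²/0.5² = 62.8, so 63, or 126 in total; 126/0.9 = 140. This matches: "Based on these assumptions a sample size of 140 adolescents (70 in each condition; G-power) is required". (The exact t version needs 128, and 128/0.9 gives 143.) The 140 stands and has no reserve: power with 63 per arm is 80.1% by the normal formula and 79.5% by the t-test.

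**2. Imbalance if allocation were unrestricted.** Assumptions: 70:70 fixed overall, ten centres of 14, four profiles of 35.
- One centre, 10:4 or worse, hypergeometric(140, 70, 14): P(X ≤ 4) + P(X ≥ 10) = 15.7%. At least one of ten, by simulation (20,000 runs): about 80%. At least one at 11:3 or worse: about 36%.
- One profile, 22:13 or worse, hypergeometric(140, 70, 35): P(X ≤ 13) + P(X ≥ 22) = 11.8%. At least one of four, by simulation: about 35%.

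**3. Upper limit of the gain from centre.** Taking out the between-centre share of variance turns d into 0.5/√(1 − ICC). With 63 per arm the normal formula gives 80.1% (ICC 0), 80.5% (0.01), 82.1% (0.05), 84.1% (0.10) and 88.1% (0.20). This ignores the degrees of freedom that centre terms use. The article gives no ICC; these values are assumed.

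**4. Simulated power, d = 0.5, ten equal centres.** The first figure in each cell comes from 3,000 runs with 10% random dropout, the second from 6,000 runs with 126 analysed.

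| ICC | Unrestricted, no centre term | Unrestricted, centre terms | Balanced by centre, centre terms |
|---|---|---|---|
| 0.02 | 80.1 / 80.1% | 76.7 / 76.5% | 79.3 / 78.7% |
| 0.05 | 79.2 / 79.7% | 77.7 / 77.9% | 80.6 / 81.5% |
| 0.10 | 79.9 / 79.7% | 80.7 / 80.3% | 83.7 / 83.3% |
| 0.20 | 80.8 / 80.3% | 84.9 / 85.9% | 87.3 / 86.8% |

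The Monte Carlo standard error of one entry is √(0.8 × 0.2/3,000) = 0.7 points, or 0.5 with 6,000 runs. Last column minus first: −0.8 and −1.4 points at 0.02; 1.4 and 1.8 at 0.05; 3.8 and 3.6 at 0.10; 6.5 and 6.5 at 0.20. A third run (8,000) gave 1.0, 1.1 and 3.4 points at 0.02, 0.05 and 0.10; a fourth gave 1 to 2.5 at 0.02 to 0.05, 4 to 5 at 0.10 and 6 to 7 at 0.20. At 0.02 the runs disagree in sign, so no gain can be claimed there.

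**5. Type I error with ten centres.** A cluster-robust standard error referred to a normal distribution (assumed; the article names no reference distribution) rejected 8.0 to 8.9% of true nulls at nominal 5%, and 9 to 10% in a further run. Fixed centre terms with a t reference rejected 4.6 to 5.5%.

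**The case against.** The strongest objection concerns allocation. A reader might infer that adolescents are allocated without restriction, that balance is left to an after-the-fact check, and that imbalance and centre noise therefore enter every comparison. The article does not support this. Randomising individuals is compatible with blocking, stratification or minimisation; a condensed article commonly leaves these to the full protocol, and a baseline comparison is also reported after stratified allocation. Chance imbalance under valid randomisation is not bias, and the standard error reflects it. Individual randomisation makes the arms comparable by centre in expectation, and the stated rule does adjust all models for variables found to differ. All of this stands, so the allocation sentence is not itself an error.

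Three further points stand in part:
- The gain is small or absent at low ICC, and the article gives no ICC.
- No loss of power or precision from a 22:13 profile split has been worked out. The case for profile rests on the article's own claims about its relevance.
- Profile is fixed before allocation only once the mean and SD behind the cut-off are fixed.

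None of this rescues the covariate rule. That rule is stated, not left out, and it makes the model depend on chance differences whichever allocation method is used.

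**Conclusion.** The concern holds as a point about the analysis. Covariates are chosen by observed imbalance and centre enters only through a standard-error correction, so two factors known before allocation are not fixed in the effect models. The stronger reading, that allocation is unrestricted and the comparisons are biased or all contaminated, is not supported.

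The size is modest. Balanced allocation with centre terms is worth about 0 to 2.5 points of power at ICC up to 0.05, about 4 at 0.10 and 6 to 7 at 0.20. These figures assume ten equal centres, 126 analysed, d = 0.5 and a continuous outcome as in the plan's own calculation. Most primary outcomes are percentages of users, so they are a guide only. The imbalance probabilities (about 80% for centre, about 35% for profile) apply only if allocation is unrestricted. With about ten clusters, a robust standard error with a normal reference may also be too liberal, which is a second reason to model centre. The sample size of 140 is unaffected. This is a cheap improvement that should be made; it does not invalidate the trial.

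**What to change.** 1. In Statistical analysis, replace the imbalance-driven rule with prespecified terms for treatment centre (fixed effect or random intercept) and personality profile in every effect model, whatever the balance table shows. Keep that table as description only.
2. State whether allocation is restricted by centre or profile. If it is not, allocate centrally in blocks of randomly varying size within centre and balance profile by minimisation, once the SURPS reference mean and SD are fixed. Fully crossed strata would be too thin: 10 × 4 = 40 cells, 140/40 = 3.5 adolescents each.

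Cost: no extra participants; a change to the analysis text and, if needed, the set-up of an allocation system. Nine degrees of freedom go to ten fixed centre terms and three to four profiles. If allocation stays unrestricted and the ICC is low, fixed centre terms lose power (about 3.5 points at 0.02 and 1.5 to 2 at 0.05 in the table), which favours restricting allocation or using a random intercept. Blocking makes allocation slightly more predictable; central allocation and random block sizes limit this.

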### Power analyses

In the present study, we aimed to show a medium effect size (cf. [14]). Power-analysis was conducted based on an average effect size of f = 0.25 [41], a 2-sided test at alpha = .05, a statistical power (1-beta) of 0.80, and 10 % loss-to-follow-up after randomization. Based on these assumptions a sample size of 140 adolescents (70 in each condition; G-power) is required. Eighteen intervention groups are required, assuming that up to a maximum of four participants will be included in intervention group.

### Intervention

Adolescents in the intervention group will receive the intervention ‘Take it personal!’ and care as usual. Adolescents will participate in one of the four versions of the intervention that address each high-risk personality trait. ‘Take it personal!’ comprises three main components: (1) psycho-education, (2) behavioral coping skills, and (3) cognitive coping skills. The first phase the intervention focuses on psycho-education regarding the participants’ personality profile and coherent problematic coping behavior, like substance abuse or aggression. In this phase, participants are motivated to become familiar with their personality profile and learn to deal with their personality through exercises. Daily life experiences and coherent physical, cognitive, and behavioral reactions will be analyzed. Participants will set individual goals, which they will try to achieve during the training. The coping skills training will engage adolescents in activities aimed at recognizing automatic thoughts. Participants will identify personality-specific thoughts that lead to problematic behavior. For example, the intervention aimed at adolescents with the personality profile ‘Impulsive’ will focus on thinking before taking action. Simultaneously, the participants will be trained to use cognitive restructuring techniques to counter such thoughts. Participants will edit a personalized ‘changing plan’ to deal differently with their problematic and risky behavior.

The intervention will involve five group sessions and six individual sessions spread across six weeks. One individual and one group session will be conducted every week, except for week 5 during which only one individual session will be offered. This week will be used to give participants extra time to practice the assigned tasks in their daily lives. Individual sessions will last 30 minutes and group sessions will last 45 minutes. During individual sessions, the trainer and participant will prepare that week’s group session. During the individual sessions, the participants will be able to pick and bring a confidant from their team of supervisors. This will increase the generalization to everyday life and ensures that participants feel prepared and secure during the group sessions.

Two qualified trainers, one psychomotor therapist and a behavioral scientist, will carry out the intervention. A psychomotor therapist will have to be present because of the exercises based on psychomotor principles while a behavioral scientist needs to be involved because of the principles of CBT and MI. Training should be provided by a behavioral scientist who is experienced with these techniques. All trainers will participate in a two-day training on the principles of CBT and MI and all sessions will be practiced. All group sessions will be carried out in the psychomotor department of the home institution. Individual sessions will be held in flexible rooms.

Each individual and group session will have the same structure. Each individual session will start by asking the participant’s confidant what he or she has learned in the last group session and what exercises they have done. Subsequently, the trainer and participant will do some exercises and assignments. In the individual session, participants will be asked to give examples from their daily lives. These examples will be used to complete exercises within the group sessions. Participants’ confidants will play a supporting role in the individual session. Afterward, the participant and trainer will prepare the next group session. All group sessions will start by offering participants some refreshments to make them feel at ease and secure. These sessions will comprise exercises, games, and psychomotor practices prepared during the individual sessions. Every group session will comprise at least one exercise from psychomotor therapy. To close the group sessions, the trainers and participants will summarize that group session together. The training will be developed according to the principles of CBT, and it will be adjusted to the cognitive capacities of adolescents with mild to borderline ID.

Adolescents assigned to the control group will receive no further intervention, but they will receive ‘care as usual’. ‘Care as usual’ will not be standardized or protocolled, but we will make an inventory of other prevention and intervention programs aimed at substance use. Most adolescents receive treatment for their own specific problems; some of them receive residential care while others receive extramural treatment. In both cases, treatment is formulated through personal goals in a so called ‘individual treatment plan’. A multidisciplinary team is involved in the treatment of each adolescent. All participating adolescents will be rewarded with a small gift.

## Data collection

During the pre-test, the participants will complete the SURPS-NL-LVG questionnaire (SURPS-NL-LVG; [40]; custom version SURPS; [42]). Based on their scores on this questionnaire, participants will be classified into one out of the four personality profiles (SS, IMP, AS, and NT).

### Outcomes

‘Take it Personal!’ aims to decrease substance use among adolescents with mild and borderline ID. We operationalized goals for limiting alcohol, cannabis, and hard drug use. The primary outcome of alcohol use will be the percentage of decrease in binge drinking, weekly use, and problematic use. The primary outcomes of cannabis use will be the percentage of decrease in lifetime cannabis use and weekly use. The primary outcome of hard drug use will be the percentage of decrease in lifetime use. These outcome measures will be assessed at baseline and two, six, and twelfth months after the intervention using the Substance Use and Misuse among Intellectually Disabled Persons Questionnaire (SumID-Q; [43]). This questionnaire is specifically developed to measure substance use among people with intellectual disabilities. Secondary outcomes are the intention to use less alcohol and/or drugs in the future [44, 31], motives for alcohol and/or drug use (Drinking Motives Questionnaire-Revised-Short Form (DMQ-R-SF) [45], and internalizing and externalizing behavioural problems measured by YSR [46]. Adolescents with mild to borderline ID are able to complete self-report instruments with some support [47]. Therefore, all measures will be supported using structured interviews.

This study examined the effectiveness of ‘Take it Personal!’ in daily practice (effectiveness trial). In this case, it is important to monitor the program fidelity [48, 49]. For this reason, we will monitor five domains: 1) adherence, 2) exposure (dosage), 3) quality of the delivery, 4) responsiveness of the participant, and 5) program differentiation (cf. [49]).

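### Six unranked primary outcomes, three unranked time points and two unranked analysis sets sit on a sample size built for one two-sided .05 comparison, with no rule for what counts as effective

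*Protocol article*

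**What the plan says.** The Outcomes section lists the primary outcomes by substance. For alcohol, "The primary outcome of alcohol use will be the percentage of decrease in binge drinking, weekly use, and problematic use". For cannabis there are two, lifetime use and weekly use. For hard drugs there is one, lifetime use. The abstract gives the same six, and neither place ranks them.

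On timing, Study design says "The intervention effects will be tested at two, six, and twelfth months after the start of the intervention". Aims and hypotheses lists the same three occasions. None is called primary.

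On analysis sets, Statistical analysis says that effects on the primary and secondary outcomes "will be tested in accordance with the intention-to-treat principle and in a completers-only framework". It does not say which set governs if the two disagree.

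The only significance level is in Power analyses: "a 2-sided test at alpha = .05", with "a statistical power (1-beta) of 0.80". The same section states "Power-analysis was conducted based on an average effect size of f = 0.25" and allows 10% for "loss-to-follow-up after randomization", arriving at 140 participants, 70 per arm.

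**The concern.** The trial is meant to answer one question: is the programme effective? The plan gives 6 x 3 = 18 primary comparisons in each analysis set and no route from them to a single answer. The sample size, by contrast, assumes one comparison.

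Two things are at stake. First, if a significant result on any outcome at any time could be presented as the primary success, the error rate behind that claim would be well above the level used in the power section. Second, a mixed picture (for example, weekly cannabis use better at 2 months, binge drinking unchanged at 12) could not be resolved by anything in the document. The completers set adds to the second problem. It is formed by what happens after randomisation, and nothing says that it cannot carry the conclusion.

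**Working it through.** **1. The plan's own sample size.** With two groups, d = 2f = 2 x 0.25 = 0.5. By the normal approximation, n per arm = 2 x (1.960 + 0.842)^2 / 0.5^2 = 62.8, rounded up to 63. Allowing for 10% loss, 63 / 0.9 = 70 per arm, or 140 in total. The stated figure is reproduced exactly, for one comparison at two-sided .05. (The t-test version needs 64 per arm, and 128 / 0.9 gives 143, close to the same.)

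**2. Number of primary tests.** Outcomes: 3 + 2 + 1 = 6. Times: 3. Within one analysis set: 6 x 3 = 18.

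**3. Error rate if any one significant result sufficed, independent tests.** 1 - 0.95^6 = 0.265 at a single time point; 1 - 0.95^18 = 0.603 over all three. Counting only results in the favourable direction (2.5% each): 1 - 0.975^6 = 0.141 and 1 - 0.975^18 = 0.366.

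**4. The same with correlated tests.** The document gives no correlations, so these are assumptions. Multivariate normal test statistics were simulated with 200,000 draws. At a single time point, six outcomes correlated at 0.5 give 21% two-sided and 10% favourable. For outcomes by three times, each cell shows two-sided / favourable only:

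| Between outcomes | Over time | 6 outcomes x 3 | 4 outcomes x 3 |
|---|---|---|---|
| 0.5 | 0.5 | 45% / 23% | 36% / 18% |
| 0.5 | 0.7 | 40% / 20% | 31% / 16% |
| 0.5 | 0.9 | 32% / 16% | 25% / 13% |
| 0.8 | 0.5 | 32% / 16% | 27% / 13% |
| 0.8 | 0.7 | 28% / 14% | 23% / 12% |
| 0.8 | 0.9 | 22% / 11% | 18% / 9% |

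The last column leaves out lifetime cannabis and lifetime hard-drug use. Once a person has used, lifetime use cannot fall, so those two outcomes may yield few informative tests.

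**5. The opposite rule, all six required.** The chance of a false claim cannot then exceed that of a single test. If each outcome had 80% power at one time point, power for all six would be 0.80^6 = 0.26 if independent, and would reach 80% only under perfect dependence.

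**6. Power if six primaries are kept at one time point.** The first Holm step uses .05 / 6 = .0083. With 63 analysed per arm and d = 0.5, power is 55% by the t-test and 57% by the normal approximation. Restoring 80% with a Bonferroni split at that level takes 97 per arm; 97 / 0.9 rounds up to 108 per arm, or 216 in total.

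**The case against.** Several objections have force.

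- **The plan never says that one significant result is enough.** This stands. A reader might infer such a rule from the unranked list, but the abstract and the hypotheses name alcohol, cannabis and hard drugs together, which could equally mean that all are needed. The rates above are therefore conditional on a rule that the document neither adopts nor excludes.
- **Two-sided rates overstate the risk of wrongly claiming benefit.** This stands. They include results that favour control, so the favourable-only figures, about half as large, are the ones to compare with a nominal 2.5%.
- **The completers analysis is not declared equal to intention-to-treat.** A reader might count 36 co-equal tests and quote 1 - 0.95^36 = 84%. The documents do not support that. Equal standing would be inferred only from the lack of a ranking, and the two sets overlap heavily. At an assumed correlation of 0.95 between sets, completers-only adds about 5 to 9 points. The inflation comes from outcomes and time points.
- **Two of the six outcomes may contribute little.** This stands, but inflation persists with the other four.
- **A journal article leaves detail to the SAP.** This is fair for the adjustment method and testing order, and their absence is not counted here. But the article itself fixes six primaries, three test occasions, two analysis frameworks and a sample size for one comparison. An adjustment elsewhere would change the power basis that this document states.

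**Conclusion.** The point holds in this form: the protocol fixes several unranked primary outcomes, time points and analysis sets, states no decision rule, and sizes the trial for one two-sided .05 comparison.

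Under an any-of rule, the chance of at least one false positive among 18 tests is about 22-45% two-sided, or about 11-23% counting only favourable results, which is roughly 4 to 9 times the nominal 2.5%. Without the lifetime-use outcomes, it is about 18-31% two-sided and 9-16% favourable for correlations over time of 0.7-0.9, rising to 36% and 18% at 0.5 over time. These figures rest on assumed correlations of 0.5-0.8 between outcomes and 0.5-0.9 over time; independence would give 60% two-sided for all 18.

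Under an all-of rule, alpha is not inflated, but the stated 80% power does not describe the trial. Under either rule the sample-size basis and the primary analysis do not match. It would go too far to say that the plan licenses a claim on any single result, or that its false-positive rate is a known number.

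**What to change.** State that the confirmatory analysis is the intention-to-treat comparison of one named primary outcome at one named time point, both chosen by the sponsor before unblinding. Make the remaining outcomes and time points supportive, and completers-only a sensitivity analysis that cannot by itself establish effectiveness. This keeps N = 140 and the stated alpha and power basis. The cost is a change of wording in the protocol, SAP and registry entry, and giving up primary status for the other outcomes.

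If several primaries are kept, test them at that one time point by intention-to-treat with Holm at overall two-sided .05, and restate the power. With all six, the first step has about 55% power with 63 analysed per arm at d = 0.5. That figure assumes a continuous outcome and independent observations, whereas the listed outcomes are percentages and the analysis section expects clustering by centre, so it would need recalculating for the actual outcomes. This option costs more than wording: on the same assumptions, 80% power at .05 / 6 takes about 216 participants.
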